#### Sample size

Sample size has been calculated taking into consideration the incidence of breast cancer in Spain, the female population of Andalusia and the formula described by Aguilar-Barojas (2005) [18]. Because of that, the number of breast cancer cases will include at least 100 women, matched with 100 control women subjected to breast reduction or augmentation. Three hospital centers will participate in the recruitment: The Unit of Mammary Pathology, General Surgery Service, University Hospital of Jaén, Spain; the Unit of Mammary Pathology, General Surgery Service, University Hospital Campus de la Salud, Granada, Spain; and Ana Moreno Clinic (Granada, Spain).

#### Biological samples

Blood, breast tissue, stool and urine samples from cases and controls will be collected. Cases women will be enrolled on the same day of the diagnosis. They will be informed about the goals and procedures of the study and their participation will be requested, and those who accept to participate in the study will sign the informed consent. They will be supplied with a kit containing: 1 thermal bag, 1 freezer block, 1 pair of latex gloves, 1 disposable bedpan, 1 spatula, and 2 disposable plastic containers for urine and stool samples.

The day of the surgery, a blood sample will be taken. Serum will be separated by centrifugation to carry out a thorough biochemical analysis and determine estrogens. Breast tissue samples will be taken during surgery, from a marginal area 3–5 cm apart from the tumor. For controls, samples will be taken from any available breast tissue during breast reduction or augmentation surgery. Both feces and urine samples, from healthy and breast cancer-affected women will be collected the day previous to mammary surgery.

### Breast and intestinal microbiota

Bacteria, archaea, fungi and viruses will be investigated in feces and breast tissue samples. Samples will be pre-treated with pathogen lysis tubes L and S (QIAGEN, Barcelona, Spain). DNA will be extracted with the QIAamp cador Pathogen Mini kit (QIAGEN, Barcelona, Spain), following the manufacturer’s directions.

#### DNA quantification

The DNA concentration of the samples will be evaluated in a NanoDrop2000c (Thermo Fisher Scientific, Waltham, MA, USA).

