#### Metagenomic library construction and sequencing

The Nextera XT DNA Library Preparation Kit (Illumina, San Diego, CA, USA) will be used for metagenomic library construction. The amplicon tagment mix (ATM) in Nextera XT, which includes the enzyme used for tagmentation, will be diluted 1:10 in nuclease-free water for library construction using 1 to 100 pg input DNA. Each 20 μL of the tagmentation reaction mixture consists of 10 μL TD buffer, 5 μL of input DNA, and 5 μL of diluted ATM. PCR cycles for library construction will be 12, 14, 17, and 20 cycles for 1000, 100, 10, and 1 pg DNA, respectively, following the manufacturer’s protocol. The manufacturer recommends 12 cycles of the PCR reaction for no less than 1 ng input DNA. Amplified libraries will be purified using AMPure XP (Agencourt, Brea, CA, USA). The quality of the purified libraries will be assessed using an Agilent High Sensitivity DNA Kit on an Agilent 2100 Bioanalyzer (Santa Clara, CA, USA). The sequencing libraries will be further quantified using the KAPA Library Quantification Kit. Metagenomic libraries will be mixed with PhiX Control v3 (Illumina) at a ratio of 9:1 and sequenced with an Illumina MiSeq Reagent Kit v3 (600 cycles).

All samples to be analyzed will be combined in a pool before starting the massive sequencing. The latter will be done with the MiSeq apparatus (Illumina).

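### The only stated measurement of extract DNA is a NanoDrop reading, which is unlikely to resolve the low-yield extracts that need the 14-, 17- and 20-cycle tiers

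*Protocol article*

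**What the plan says.** Under 'DNA quantification', the protocol article gives a single sentence on measuring extracted DNA: "The DNA concentration of the samples will be evaluated in a NanoDrop2000c". It states no reading limit, no expected yield from stool or breast tissue, and no second assay.

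Under 'Metagenomic library construction and sequencing', the tagmentation enzyme "will be diluted 1:10 in nuclease-free water for library construction using 1 to 100 pg input DNA". The reaction contains "10 μL TD buffer, 5 μL of input DNA, and 5 μL of diluted ATM". The cycle rule follows: "PCR cycles for library construction will be 12, 14, 17, and 20 cycles for 1000, 100, 10, and 1 pg DNA, respectively". The article adds: "The manufacturer recommends 12 cycles of the PCR reaction for no less than 1 ng input DNA".

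Two further checks appear in that section: a Bioanalyzer quality check on the purified libraries, and then "The sequencing libraries will be further quantified using the KAPA Library Quantification Kit". Both act on DNA that has already been amplified.

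**The concern.** The cycle rule needs the input mass of each extract before PCR. The one instrument named for that is a microvolume UV spectrophotometer, and the masses in the rule correspond to very dilute solutions. If an extract is too dilute to be read, its tier and its enzyme-to-DNA ratio are chosen from a reading that carries little information.

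The consequences would reach the microbiota data. A poorly matched enzyme ratio can give failed or over-fragmented libraries, and 'Data processing for metagenomic libraries' discards reads shorter than 100 nucleotides. More cycles than needed add PCR duplicates and amplification bias. Taxonomic assignment uses a minimum support of 1, so a taxon can rest on very few reads. As described, the plan also does not record input mass or cycle number per library, so an imbalance in these between cases and controls could not be checked afterwards.

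**Working it through.** **Inputs from the article.** The input volume is 5 µL. The tiers are 1000, 100, 10 and 1 pg, with 12, 14, 17 and 20 cycles. The stated condition for 12 cycles is at least 1 ng (1000 pg).

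**Input that is assumed.** The article gives no lower reading limit L for the instrument. I take 1 to 5 ng/µL as a working range and 0.2 ng/µL as a favourable case.

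**Step 1: concentration needed at each tier.** Concentration = mass / 5 µL. For example, 100 pg / 5 µL = 20 pg/µL = 0.02 ng/µL.

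**Step 2: shortfall.** Shortfall = L / concentration. For example, at L = 1 and 100 pg: 1 / 0.02 = 50.

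| Input mass | Cycles | Concentration (ng/µL) | Shortfall, L = 0.2 | Shortfall, L = 1 | Shortfall, L = 5 |
|---|---|---|---|---|---|
| 1000 pg | 12 | 0.2 | 1 | 5 | 25 |
| 100 pg | 14 | 0.02 | 10 | 50 | 250 |
| 10 pg | 17 | 0.002 | 100 | 500 | 2,500 |
| 1 pg | 20 | 0.0002 | 1,000 | 5,000 | 25,000 |

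**Step 3: can dilution rescue the rule?** For a readable extract, yes. An extract at 1 ng/µL holds 1 × 5 × 1000 = 5,000 pg in 5 µL. One at 5 ng/µL holds 25,000 pg. Either can be measured and then diluted to a tier: 5- to 25-fold for 1000 pg, 50- to 250-fold for 100 pg.

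**Step 4: which extracts need the higher-cycle tiers?** By the article's own condition, 1 ng or more in the reaction qualifies for 12 cycles. In 5 µL that is 1000 pg / 5 µL = 0.2 ng/µL. An extract at or above 0.2 ng/µL therefore already qualifies for 12 cycles and has no evident need for 14, 17 or 20. The extracts that do need those tiers are below 0.2 ng/µL, and so are unreadable for any L of 0.2 ng/µL or more. Dilution does not help them, because there is no reliable reading to dilute from.

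**Step 5: do the later checks close the gap?** No. The Bioanalyzer and KAPA steps measure finished libraries, after the cycle number has been used.

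**The case against.** The strongest objection is that nothing in the article says extracts are read at picogram concentrations. A laboratory could measure a concentrated extract and dilute it. No host-DNA depletion is described, so breast extracts would carry human DNA and could well be readable. The sentence on 1:10 enzyme dilution can be taken as the low-input case and not as a target for every sample. This stands as far as it goes: it removes readable extracts from the concern. It does not reach extracts under 0.2 ng/µL, and the stated rule has three tiers that serve exactly those.

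A second objection is that safeguards exist. The Bioanalyzer check should reveal failed or badly fragmented libraries, and PCR duplicates are removed in data processing. This limits the harm, but amplification bias could remain, and neither step corrects the choice of tier.

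A third is that bench detail is commonly left out of a condensed article. That would answer a mere omission. Here the article gives DNA quantification its own section, names one instrument, and then states a rule that this instrument is unlikely to serve at its lower tiers. It is still fair to say that the article does not state outright that the NanoDrop value alone sets the tier.

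A reader might infer two stronger things. One is that the cycle rule cannot be applied correctly at all. The dilution argument defeats that. The other is that the error differs between cases and controls, since 'Biological samples' takes case tissue 3–5 cm from the tumour and control tissue from whatever is available at surgery. A difference is possible, but the article gives no yields, so it cannot be asserted. For the same reason no misassignment rate can be computed: it would need yields and a reading error that the article does not give.

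**Conclusion.** The concern holds in a limited form, with medium confidence, and should be acted on. The stated measurement does not fit the lower part of the stated cycle rule. The size depends on an assumed reading limit. Over 1 to 5 ng/µL the tier concentrations are 5 to 25 times too low at 1000 pg, 50 to 250 times at 100 pg and 5,000 to 25,000 times at 1 pg. At 0.2 ng/µL the 1000 pg tier becomes just readable, while inputs of 1 to 100 pg remain 10 to 1,000 times below the limit. The qualitative conclusion therefore does not hinge on the exact limit, provided that it is 0.2 ng/µL or higher.

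How many extracts are affected is unknown. Breast tissue with low DNA yield is where the problem would mainly arise, and stool may be largely free of it. The documents support neither a claim that the rule fails for all samples nor a claim of differential error between the groups.

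**What to change.** In 'DNA quantification', base library input on a high-sensitivity fluorometric assay specific to double-stranded DNA, and use qPCR for extracts below that assay's limit. Keep the NanoDrop for purity ratios.

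In 'Metagenomic library construction and sequencing', state that the cycle tier and enzyme dilution are assigned from that value, and say whether and when extracts are diluted to a target input. Record input mass and cycle number for every library, so that their balance between cases and controls can be checked in the microbiota comparisons.

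The cost is a reagent kit, a few microlitres of each extract and a short addition to the laboratory procedure. 'Trial status' says that enrolment and analysis continue, so the change can still help samples not yet processed.

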#### Metagenomic library construction and sequencing

The Nextera XT DNA Library Preparation Kit (Illumina, San Diego, CA, USA) will be used for metagenomic library construction. The amplicon tagment mix (ATM) in Nextera XT, which includes the enzyme used for tagmentation, will be diluted 1:10 in nuclease-free water for library construction using 1 to 100 pg input DNA. Each 20 μL of the tagmentation reaction mixture consists of 10 μL TD buffer, 5 μL of input DNA, and 5 μL of diluted ATM. PCR cycles for library construction will be 12, 14, 17, and 20 cycles for 1000, 100, 10, and 1 pg DNA, respectively, following the manufacturer’s protocol. The manufacturer recommends 12 cycles of the PCR reaction for no less than 1 ng input DNA. Amplified libraries will be purified using AMPure XP (Agencourt, Brea, CA, USA). The quality of the purified libraries will be assessed using an Agilent High Sensitivity DNA Kit on an Agilent 2100 Bioanalyzer (Santa Clara, CA, USA). The sequencing libraries will be further quantified using the KAPA Library Quantification Kit. Metagenomic libraries will be mixed with PhiX Control v3 (Illumina) at a ratio of 9:1 and sequenced with an Illumina MiSeq Reagent Kit v3 (600 cycles).

All samples to be analyzed will be combined in a pool before starting the massive sequencing. The latter will be done with the MiSeq apparatus (Illumina).

#### Data processing for metagenomic libraries

Metagenomic reads will be subjected to adaptor clipping and quality trimming using Trimmomatic v0.33 [19]. The first three nucleotides with quality scores less than 20 will be cut from the 3′ and 5′ read ends. Reads will be processed using a sliding window method, cutting once the average quality within the window (4 base) fell below the threshold (Q20). Reads with a length of fewer than 100 nucleotides will be then removed. Low-complexity reads will be filtered out using PRINSEQ version 0.20.4 [20]. PCR duplicates will be removed with Picard version 2.8.0 (http://broadinstitute.github.io/picard). The processed high-quality and clean reads in each library will be used in subsequent analyses. In the community analysis based on metagenomic sequences, small subunit (SSU) rRNA gene sequences will be identified using Metaxa2 software [21]. Taxonomy assignments will be performed based on the results of a BLAST search against the SILVA123 database [22], using the MEGAN program [23] with the following settings: Min Support 1, Min Score 50, Max Expected 1xe^− 5^, Top Percent 10.0. SSU rRNA gene community compositions were compared among the metagenomic libraries.

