### Statistical analysis

Relative abundance of the microbes will be expressed as median ± range. Differences among microbes will be calculated by the *U*-Mann de Whitney. Intestinal and mammary microbiota clusters will be calculated by an analysis of principal components made with the bioinformatic data. Those data will be normalized between 0 and 1, and the Euclidean distance will be evaluated. A permutation ANOVA (PERMANOVA) will be carried out with the PRIMER 7 software. Finally, a tree diagram will be built for each evaluated group based on the different taxonomic scales.

For metabolomic statistical analysis and data display purposes, any missing values will be assumed to be below the limits of detection, and these values will be imputed with the compound minimum (minimum value imputation). The data will be tested for variance homogeneity, and if there were unequal variances, the data will be log-transformed. The statistical analysis of the data will be performed using Array Studio (OmicSoft, NC, USA) and proprietary software from Metabolon. A t-test for equality of the means will be carried out between the intestinal and mammary microbiota and for each metabolite to determine differences. A *p*-value 0.05 will be considered statistically significant. A one-way ANOVA, assuming homogeneity of variance, will be used to determine whether at least two unknown means are all equal or at least one pair of means is different. In case that the variances were unequal, a Welch-ANOVA will be performed. The false discovery rate (q-value) will be calculated to take into account the multiple comparisons that normally occur in metabolomics-based studies, thus estimating the reliability of the results. A q-value 0.1 will be considered statistically significant.

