Random forest (RF) is a supervised classification technique based on an ensemble of decision trees [35] with several advantages. It makes no parametric assumptions, and variable selection is not needed. It does not overfit, and it is invariant to transformation. In RF analysis, it is not necessary to cross-validate or do a separate test set to obtain an unbiased estimate of the test set error. A “variable importance” measure will be computed to determine which variables (metabolites) make the largest contribution to the classification. The mean decrease in accuracy (MDA) will be used as this metric and will be determined by randomly permuting a variable, running the observed values through the trees, and then reassessing the prediction accuracy. If a variable were not significant, then this procedure will have little change in the accuracy of the class prediction (permuting random noise will give random noise). By contrast, if a variable is relevant for the classification, the prediction accuracy will drop after such a permutation, which will be recorded as the MDA. Thus, the RF analysis provides an “importance” rank ordering for biochemicals [35].

Participants will be grouped into tertiles of urinary EDC levels based on their distributions among the controls. Odds ratios and 95% confidence intervals (CIs) for breast cancer comparing the second and third tertiles with the first tertile will be estimated using logistic regression models. Further, associations of participant characteristics with urinary EDC levels, estrogens and estrogen metabolites and fecal microbiome measures will be evaluated by using general linear models and testing either for differences across categories or for trends across categories. Linear regression models will also be used to evaluate associations of each steroid measure with measures of the diversity of the fecal microbiome, abundance and with taxonomic groups at phylum and family levels, adjusting by covariates.

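### With a one-read detection limit and no account taken of SSU read number, rare-taxon rank tests and richness-type fecal diversity depend on sequencing depth, although relative abundance protects the common taxa

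*Protocol article*

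**What the plan says.** The protocol article, under Data processing for metagenomic libraries, fixes the pipeline closely: trimming rules, a minimum read length, duplicate removal, database version and classifier settings. Three of its statements matter here.

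- After cleaning, "The processed high-quality and clean reads in each library will be used in subsequent analyses".
- Only part of each library feeds the taxonomy: "small subunit (SSU) rRNA gene sequences will be identified using Metaxa2 software".
- The classifier settings include "Min Support 1, Min Score 50", so one read is enough to call a taxon present.

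Under Metagenomic library construction and sequencing, PCR cycles run from 12 to 20 as input DNA falls from 1000 to 1 pg, libraries are quantified, and "All samples to be analyzed will be combined in a pool before starting the massive sequencing". Equimolar pooling is not mentioned.

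Under Statistical analysis, "Relative abundance of the microbes will be expressed as median ± range" and taxa are compared by the Mann-Whitney U test. For the ordination and PERMANOVA, "Those data will be normalized between 0 and 1, and the Euclidean distance will be evaluated"; whether shares or counts are scaled is not said. Linear regression then relates "associations of each steroid measure with measures of the diversity of the fecal microbiome", and also taxon abundance at phylum and family level, with adjustment for covariates that are not listed. No step in these sections refers to the number of assigned reads.

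**The concern.** A sample with more assigned SSU reads shows more taxa and fewer zeros, whatever its biology. Dividing by the total corrects the expected share of a taxon but not the chance that the taxon is seen at all, and a rank test responds to the pattern of zeros.

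Two consequences follow. If read number differs between cases and controls, rare taxa can appear to differ when the communities are the same, and such a result would look like the association the study is looking for. If read number varies only at random, it adds noise to any richness-type diversity measure, and the steroid regressions lose power.

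Uneven SSU depth is plausible from the document: the range of input DNA is wide, only SSU reads count, and all samples share one pool. A difference by group is plausible in breast tissue, because the Biological samples section takes case tissue 3-5 cm from the tumor and control tissue from wherever it is available.

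**Working it through.** The document gives no read depth, so every depth below is an assumption. Its only relevant design figure is the group size of at least 100 cases and 100 controls; there is no stated depth or error rate to reproduce. A two-sided 0.05 level is assumed for taxa, since the article states it only for metabolites.

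**1. Detection on one read.** P(seen) = 1 - (1 - p)^D, for true share p and D assigned reads.

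- p = 1%: 0.993 at D = 500; 1.000 at D = 1000.
- p = 0.1%: 1 - 0.999^500 = 0.39; 1 - 0.999^1000 = 0.63.

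Common taxa are seen either way. For rare taxa, doubling the reads changes the proportion of zeros markedly.

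**2. Null simulation, 200 taxa.** 100 v 100 women from the same community, log-SD of depth 0.5, three levels of between-woman variation (Dirichlet concentration 50, 1000, or none), 60 runs each. Entries are rejection rates at 0.05, as ranges over the three levels. The Monte Carlo standard error at 0.05 is √(0.05 × 0.95/60) = 0.028.

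| Mean SSU reads | 1000 v 1000 | 1000 v 500 | 1000 v 250 |
|---|---|---|---|
| Mann-Whitney on shares, 5% and 1% taxa | 0.03-0.12 | 0.03-0.08 | 0.07-0.13 |
| Mann-Whitney on shares, 0.1% taxon | 0.00-0.07 | 0.10-0.40 | 0.17-0.95 |
| Proportion of all taxa with p<0.05, shares | 0.05 | 0.07-0.23 | 0.18-0.64 |
| PERMANOVA, 0-1 scaled shares | 0.07-0.08 | 0.02-0.17 | 0.03-0.60 |
| PERMANOVA, 0-1 scaled counts | 0.02-0.08 | 1.00 | 1.00 |

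On raw counts, Mann-Whitney for the 5% and 1% taxa rejected in 0.80-1.00 of runs at 1000 v 500, so working with shares is a real protection. The larger figures for rare taxa arise when women vary little from one another; a separate 200-run set at 1000 v 500 gave only 0.08 for the 0.1% taxon.

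**3. Null simulation by depth ratio, relative abundances, 100 v 100.** Two sets of runs, one of them with 80 families, depth geometric SD 2 and median 50-1000 SSU reads. Percentage of taxa with p<0.05:

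| Depth ratio | 80 families | Second set |
|---|---|---|
| 1.5 | 7-11% | 7-11% |
| 2 | 13-22% | 9-19% |
| 3 | 28-41% | 11-39% |

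After subsampling to a common depth, both sets gave 3-6%. In the second set, taxa above 1% stayed near nominal except at very low depth.

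**4. Power of the steroid-diversity regression.** 200 women, true correlation 0.3, no group difference in depth, depth geometric SD 2-3. For richness, power was 37-79% without and 82-94% with log read number as a covariate. A second set gave 31-87% and 82-93%, and left Shannon unchanged.

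A hand check shows why. If a fraction s of the variance of observed richness comes from depth, the observable correlation is 0.3 × √(1 - s), and power is about Φ(atanh(r) × √197 - 1.96).

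- s = 0: r = 0.30, Φ(4.34 - 1.96) = 0.99.
- s = 0.5: r = 0.212, Φ(3.02 - 1.96) = 0.86.
- s = 0.85: r = 0.116, Φ(1.64 - 1.96) = 0.37.

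The covariate removes s. Read-sampling noise remains, so the simulated power stays below 0.99.

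**The case against.** The strongest reply is that the sentence on clean reads closes the quality-control steps; it says which reads survive, not that depth is ignored. A condensed article may leave a depth rule to the full protocol or analysis plan, and the linear models already adjust for unnamed covariates. This stands to the extent that absence alone is no error. What remains is that a closely specified pipeline fixes one-read detection and then names analyses that depend on it.

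Second, the analysis variable is relative abundance. This also stands, and it limits the bias mainly to rare taxa. A reader might infer that taxon tests in general are driven by depth; the figures for 1% and 5% taxa do not support that.

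Third, a reader might infer that case-control comparisons of richness will be wrong almost every time. Under unequal depth such a test does reject in most runs (0.785 at 1000 v 750 reads, 1.00 at 1000 v 500), but the article plans no case-control test of diversity. Its diversity analysis concerns stool and steroids, where depth is mainly noise unless it is related to steroid levels.

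Fourth, no group difference in depth is documented, and library quantification and input-scaled PCR cycles may reduce one. The tissue-site argument applies to breast tissue only; no reason for a difference in stool has been identified.

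Finally, compulsory subsampling has costs. With a median of 50 reads and geometric SD 2, the 10th percentile is 50 × exp(-1.28 × 0.693) ≈ 21 reads. Dropping the lowest 10% of libraries breaks about 1 - 0.9² = 19% of matched pairs if losses are independent, and up to 20%. In breast tissue a low SSU yield may itself reflect low microbial load. This objection stands and shapes the remedy.

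**Conclusion.** The concern holds in a limited form. Followed as written, the plan lets rank tests of rare taxa and richness-type fecal diversity depend on assigned SSU read number.

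For rare taxa the bias is conditional on a case-control difference in read number, which is plausible in breast tissue but not shown. At assumed ratios of 1.5, 2 and 3, the proportion of taxa falsely significant is 7-11%, 9-22% and 11-41%, against a nominal 5%. Common taxa stay near nominal except at very low depth. For fecal richness no group difference is needed: random depth variation alone cut power to 31-87%, against 82-94% with the covariate, at an assumed true correlation of 0.3. If the diversity index is Shannon, the gain is negligible.

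The unspecified 0-1 scaling is a separate ambiguity: applied to counts it would make PERMANOVA depth-driven (1.00 at a twofold ratio); applied to shares it stays near nominal in most twofold settings.

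All of these sizes rest on assumed depths, community structure and between-woman variation.

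**What to change.** In the Statistical analysis section:

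- Add log(assigned SSU reads) as a covariate in the linear models for fecal diversity and taxon abundance. Cost: one degree of freedom.
- State that the 0-1 scaling before Euclidean distance and PERMANOVA is applied to relative abundances, not counts. Cost: one sentence.
- Report assigned SSU read number by case status, separately for stool and breast tissue, so that readers can see whether the condition for bias is met. Cost: one small table.
- Repeat the rare-taxon Mann-Whitney tests at a common subsampled depth as a sensitivity analysis, not as the only analysis. Cost: some computing; within that analysis, discarded reads, lost shallow libraries and broken matched pairs. Agreement with the main result is reassuring. Disagreement in breast tissue needs care, because low yield may be real.

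No new samples or assays are needed, and the trial is still enrolling.

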**Methods:**

We describe a case-control clinical study that will be performed in women between 25 and 70 years of age. Cases will be women diagnosed and surgically intervened of breast cancer (stages I and II). Women with antecedents of cancer or advanced tumor stage (metastasis), or who have received antibiotic treatment within a period of 3 months prior to recruitment, or any neoadjuvant therapy, will be excluded. Controls will be women surgically intervened of breast augmentation or reduction. Women with oncological, gynecological or endocrine history, and those who have received antibiotic treatment within a period of 3 months prior to recruitment will also be excluded. Blood, urine, breast tissue and stool samples will be collected. Data regarding anthropometric, sociodemographic, reproductive history, tumor features and dietary habits will be gathered.

Metabolomic studies will be carried out in stool and breast tissue samples. Metagenomic studies will also be performed in stool and breast tissue samples to ascertain the viral, fungal, bacterial and archaea populations of the microbiota. Quantitation of estrogens, estrogen metabolites and EDCs in samples of serum, urine and breast tissue will also be performed.

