**Discussion:**

This is the first time that the contribution of bacteria, archaea, viruses and fungi together with their alteration by environmental contaminants to the risk of breast cancer will be evaluated in the same study. Results obtained could contribute to elucidate risk factors, improve the prognosis, as well as to propose novel intervention studies in this disease.

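### Viruses are one of four stated microbial targets, but the only taxonomic analysis described works on rRNA genes, which viruses lack

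*Protocol article*

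**What the plan says.** Viruses appear as a target in three places in the protocol article:

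- The Abstract (Methods) gives the purpose of the metagenomic work as "to ascertain the viral, fungal, bacterial and archaea populations of the microbiota".
- The Abstract (Discussion) rests the study's novelty on evaluating "the contribution of bacteria, archaea, viruses and fungi together with their alteration by environmental contaminants" in one study.
- The section Breast and intestinal microbiota states: "Bacteria, archaea, fungi and viruses will be investigated in feces and breast tissue samples".

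The Background supports this interest by citing links between breast cancer and two viruses, Epstein-Barr virus and human papilloma virus.

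The laboratory steps are DNA-based. "DNA will be extracted with the QIAamp cador Pathogen Mini kit", and "The Nextera XT DNA Library Preparation Kit (Illumina, San Diego, CA, USA) will be used for metagenomic library construction".

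The section Data processing for metagenomic libraries then sets out the community analysis. After trimming and filtering, "small subunit (SSU) rRNA gene sequences will be identified using Metaxa2 software". Next, "Taxonomy assignments will be performed based on the results of a BLAST search against the SILVA123 database", with MEGAN settings listed. The section closes: "SSU rRNA gene community compositions were compared among the metagenomic libraries".

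**The concern.** The target and the method do not match. Selecting SSU rRNA gene sequences and classifying them against an rRNA reference suits organisms that have ribosomes. Viruses have no ribosomal RNA genes, so a viral read has nothing for this step to recognise.

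At stake is one of the four organism groups the study says it will characterise, and with it the claim that all four will be evaluated together. If the analysis is run as described, the study will have no viral variable to relate to case status, to endocrine-disruptor exposure or to estrogens, although the abstract tells readers that viruses are covered.

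**Working it through.** No arithmetic applies. The check follows each of the four target groups through the described steps and looks for any point at which it could receive a taxonomic label.

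1. **Extraction and library** (Breast and intestinal microbiota; Metagenomic library construction and sequencing). DNA is extracted and total DNA is made into libraries. These are not rRNA amplicon libraries. DNA from all four groups, including DNA viruses, can be present in the reads. No RNA extraction or reverse transcription is described.

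2. **Read cleaning** (Data processing for metagenomic libraries). Trimming, length and complexity filters and duplicate removal are not specific to any group. Viral DNA reads can survive them.

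3. **Selection for the community analysis** (same section). Metaxa2 identifies SSU rRNA gene sequences. Bacteria and archaea carry a 16S gene and fungi an 18S gene, so all three can be recognised. Viruses carry neither.

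4. **Taxonomy** (same section). SILVA123 is the only reference named, and no viral reference appears. The quantity compared between libraries is the SSU rRNA gene composition.

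5. **Other identification steps.** The only other one is in the section on phosphorylated histone 2AX, where 16S PCR identifies cultured bacterial colonies. It covers bacteria only.

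6. **Statistical analysis.** Relative abundances of microbes are summarised and compared, and fecal diversity and phylum- and family-level groups enter regressions. No separate viral measure is defined, so nothing here supplies one from another source.

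| Group | SSU rRNA gene | Described route to a result |
|---|---|---|
| Bacteria | 16S | Yes |
| Archaea | 16S | Yes |
| Fungi | 18S | Yes |
| Viruses | None | None |

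Three of the four stated groups can be classified. For the fourth, the article contains no viral classifier, viral reference, assembly step or virus-specific PCR.

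**The case against.** The best defence is that this is a condensed article and the viral analysis may sit in the full protocol. The article says that the cleaned reads go forward to later analyses, in the plural, and presents the SSU step as belonging to the community analysis only. That leaves room for a viral analysis, but it does not remove the point. The section is not condensed here: it fixes software versions, quality thresholds, the database release and the MEGAN settings. The only taxonomic analysis that follows is the rRNA one, and it cannot serve a target stated in three places.

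Other parts of the defence stand. They mark off stronger conclusions that a reader might draw and that the document does not support:

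- **That viral data are lost.** The article says which sequences Metaxa2 identifies, not that the remaining reads are destroyed. DNA-virus reads may well be in the data.
- **That SSU profiling is wrong for the other groups.** Profiling bacteria, archaea and fungi from SSU reads in shotgun data is a coherent choice. Setting other reads aside is how that choice works.
- **That breast tissue profiles will rest on very few reads.** The article says samples are pooled, but gives neither the number of sequencing runs nor the yield, the SSU share or the human share of reads. Depth cannot be judged from it.
- **That failing to cover RNA viruses contradicts the aims.** The article never claims RNA viruses, and both viruses named in the Background are DNA viruses. The scope should be stated, but the DNA workflow is not in itself an error.
- **That the study would report a false absence of association for viruses.** No viral variable is defined, so there would be no zero count to test. The foreseeable outcome is no viral result.

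**Conclusion.** The concern holds in a limited form. No described step can identify or quantify viruses, so the viral aim and the claim to evaluate bacteria, archaea, viruses and fungi together cannot be met as written.

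The gap covers one of four organism groups, in both stool and breast tissue. The bacterial, archaeal, fungal, metabolomic, endocrine-disruptor and estrogen analyses do not depend on it.

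The conclusion rests on one fact from outside the document, the basic biology that viruses have no rRNA genes, and on reading the data-processing section as the taxonomic analysis that will be run. If the full protocol holds a viral classification step, the article needs only to say so.

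**What to change.** Keep the SSU rRNA route for bacteria, archaea and fungi, and add a viral branch to Data processing for metagenomic libraries:

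1. Remove human reads from the quality-filtered shotgun reads.
2. Classify the remaining reads against a named reference and release that includes viral genomes.
3. Define the viral abundance measure, including its denominator, and say in Statistical analysis how it will be compared between cases and controls.
4. State that extraction and libraries are DNA-only, so the scope is DNA viruses.

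If this branch will not be added, remove viruses from both parts of the Abstract and from Breast and intestinal microbiota, so that the aims and the novelty claim match what will be analysed.

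The cost is extra bioinformatic work on the same reads and a narrower stated scope. No new samples or assays are needed for DNA viruses. Viral reads in breast tissue may still prove sparse, and the plan should say how that would be reported. Trial status describes enrolment and data analysis as continuing, so the branch should be fixed before the viral data are examined.
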